**English translation of the study protocol**

2 Objective of the study

  To test the effectiveness of antibiotic therapy with Josamycin in case of positive PCR for Ureaplasma spp. and / or Mycoplasma hominis to reduce spontaneous prematurity in asymptomatic patients who perform amniocentesis in the second trimester.

3 Type of study

This is a therapeutic trial in a multicenter randomized placebo double blind study.

Seven maternities with a prenatal diagnosis center and a bacteriology laboratory will participate in the study.

Monitoring and randomization will be provided by the URC Henri Mondor University Hospital.

Packaging of the drug and placebo will be provided by a Bayer laboratory. Lot numbering, dispatch to the central pharmacies of the investigating centers, returns, destruction and stability studies of the active ingredient will be carried out by the AGEPS clinical trial unit.

The methodological and statistical aspect is provided by the Epidemiological Research Unit on the Health of Women and Children (INSERM U 149).

4 Population studied

The study population will be composed solely of patients who have amniocentesis during pregnancy in order to perform a prenatal diagnosis. Indeed, there is no invasive procedure performed for the study and no additional risk of bleeding for the patient. Only 3 ml of amniotic fluid will be reserved for the study on the total quantity taken normally in the patient who is variable (between 15 and 40 ml) according to the objectives of the prenatal diagnosis. This additional 3 ml has no impact on the risk of fetal loss secondary to amniocentesis that is attributable to the puncture itself and not to the amount removed.

It is possible that the study population is different from the general population. In fact, patients with amniocentesis are older and present a risk of obstetric complications during pregnancy, which may be different from younger women, particularly with regard to hypertension and preeclampsia. Nevertheless, there is no evidence of an increased risk of premature birth due to age.

Finally, amniocentesis leads to an increased risk of fetal loss estimated at 0.6 to 1% during pregnancy, 32 but this does not distort comparability between groups since all patients have amniocentesis.

5 Inclusion criteria

 Major patient (≥ 18 years old)

 Speaking and understanding French

 Patient affiliated with social security or a similar scheme

 Having an indication of amniocentesis for karyotype analysis and normal morphological ultrasound (apart from minor signs of trisomy 21)

 With amniocentesis a clear amniotic fluid (uncontaminated by maternal blood)

 whose gestational age is between 15 and 20 weeks

 Not having known allergy to macrolides

 Patient followed during her pregnancy in an investigative center

 giving informed and signed consent

6 Exclusion criteria

 Minor patient

 Not understanding French

 Having an allergy to macrolides

 Having a multiple pregnancy

 Morphological abnormality on ultrasound (apart from minor signs of trisomy 21)

 Patient refusing to participate in the trial for any reason

 Known intolerance to Lactose

7 Factor studied: PCR for Mycoplasma hominis and Ureaplasma spp.

In order for the PCR procedure to be homogeneous, it will be completely performed in the bacteriology laboratory of Cochin. This has a direct implication on the centers that can be included in the study. The distance plays indeed a major role, an important distance of the centers would prevent a fast routing essential for the study. On the other hand this would require special transport conditions (freezing at -80 ° C) that would make the costs very high.

The search for Mycoplasma hominis and Ureaplasma spp. (U. parvum and U. urealyticum) will be performed by PCR on the amniotic fluid after extraction of the DNA. Briefly, the DNA will be extracted from 200 μl of each sample using the Qiagen extraction kit. The PCRs will be performed using primers specific for highly conserved areas found in the urease gene for Ureaplasma spp. and in the 16S RNA gene for M. hominis (Table VII). The sequences of these primers are described, evaluated and published in several studies 24, 26-28.

The specificity of the amplification product will be evaluated by an ELISA technique during which the amplicons will be denatured, biotinylated and evaluated by measuring the optical density of a colorimetric reaction. The amplified products will also be characterized by their size, after migration on agarose gel containing BET. For Mycoplasma hominis the fragment obtained will also be subjected to a digestion in enzymatic allowing a more specific identification. The PCR technique may also allow the distinction between the two recently identified Ureaplasma species (U. parvum and U. urealyticum).

8 Antibiotics used

The desired site of action of antibiotics is the deciduous, the chorion and the amnion. Indeed, a positive PCR in the amniotic fluid essentially testifies to an attack of these choriodecidural tissues and those should be preferentially concerned by the antibiotherapy.

The target bacteria for antibiotic therapy are Mycoplasma hominis and Ureaplasma spp.

Tetracyclines, macrolides and related drugs (lincosamides including clindamycin) and fluoroquinolones are the main families of antibiotics active against these bacteria.33 The antibiotics that can be used are macrolides and lincosamides because tetracyclines and fluoroquinolones are contraindicated during pregnancy. pregnancy and in children.

Ureaplasma spp. is sensitive to macrolides but resistant to lincosamides. In contrast, Mycoplasma hominis is resistant to 14- and 15-carbon macrolides such as erythromycin but is sensitive to certain 16-carbon macrolides (josamycin and midecamycin) and lincosamides. Among the different macrolides, josamycin represents the best compromise for its activity on the two bacterial species with minimum inhibitory concentrations for Mycoplasma hominis <1mg / L and for Ureaplasma spp. <2mg / L (Table VIII) 34.

A dosage of two grams per day of josamycin for 10 days would allow sufficient intratissue concentrations to be active on mycoplasmas for a sufficiently long time to reduce the risk of recurrence.

12 Criteria for judgment

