12.1 Primary judgment criterion

Occurrence of premature delivery between 22 and 37 weeks

12.2 Secondary judgment criteria.

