12.2.1 Obstetrical

Prenatal:

• Late miscarriage occurred between 16 and 22 weeks

• Premature delivery  34, 32, 28 SA.

• Hospitalization for the threat of premature labor

• Number of days of hospitalization for threat of preterm birth

• Premature rupture of the membranes before 37 SA

• Occurrence of chorioamnionitis defined by two of the following criteria: maternal temperature> 38 ° C, uterine contractions, foul leucorrhea, fetal tachycardia> 160 bpm, CRP> 10 mg / L.

During work :

• Hyperthermia> 38 ° C

• Fetal tachycardia> 160 bpm

In the postpartum:

• Hyperthermia> 38 ° C for more than 24 hours

• Need for antibiotic treatment for more than 48 hours

Neonatal 12.2.2

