13.3 Sending the sample to the bacteriology laboratory

The amniotic fluid samples for research (PCR for Mycoplasma hominis and Ureaplasma spp) will be stored at 4 ° C in a specific medium for a maximum of 3 days and delivered by the APHP coureur to the bacteriology laboratory. Cochin hospital where they will be received by the laboratory technician.

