13.4 Selection of patients for the therapeutic trial

The result of the PCR will be transmitted the same day by fax to the investigating doctor (and the URC Henri Mondor).

If the PCR is negative, the patient will be informed of the result by telephone. The doctor will inform her that she will not participate in the therapeutic trial but that the follow-up of her pregnancy will be carried out in a traditional way and that the data collected during this follow-up will be used for research purposes (until delivery and her maternity leave). The patient will be reviewed by the investigating physician during scheduled visits as part of the normal follow-up of her pregnancy. Since no visit is done specifically for the research, it does not entail any additional cost for the patient.

If the PCR is positive for Ureaplasma spp. and / or Mycoplasma hominis, the patient will be contacted by the clinical research technician who will propose an appointment with the doctor to announce this result to him and propose him the batch of treatment.

The doctor will make sure that the patient is willing to continue the research and participate in the therapeutic trial.

If the patient does not wish to participate in the therapeutic trial, the patient will be out of the study. The monitoring of her pregnancy will be ensured according to the current practices of the service, and in the best interest for the patient and her future child.

If the patient wishes to continue her participation, an appointment will be offered for a treatment dispensation visit (if telephone contact). During this visit, the patient will be randomized in the group (Josamycin) or in the group (Placebo). Neither the doctors nor the patients will know in which group they belong. Patient travel expenses will be borne by the research sponsor.

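### The primary endpoint is not limited to spontaneous preterm delivery and has no rule for terminations, in a trial that recruits through karyotyping and randomises without regard to the result

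*Protocol*

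**What the plan says.** **Eligibility.** Protocol section 5 admits women "Having an indication of amniocentesis for karyotype analysis and normal morphological ultrasound". The requirement is the indication, not a normal result. The one fetal exclusion in section 6, apart from multiple pregnancy, is "Morphological abnormality on ultrasound (apart from minor signs of trisomy 21"; the karyotype is not mentioned.

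**Path to randomisation.** Section 13.3 stores the fluid "in a specific medium for a maximum of 3 days". Section 13.4 continues: "The result of the PCR will be transmitted the same day by fax to the investigating doctor". A woman with a positive PCR who agrees to go on attends a dispensing visit: "During this visit, the patient will be randomized in the group (Josamycin) or in the group (Placebo". Nothing in this sequence waits for the karyotype or refers to it.

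**Objective and endpoints.** Section 2 sets out "to reduce spontaneous prematurity in asymptomatic patients who perform amniocentesis in the second trimester". The primary criterion in section 12.1 is "Occurrence of premature delivery between 22 and 37 weeks", without the word spontaneous. Section 12.2.1 lists "Late miscarriage occurred between 16 and 22 weeks" as a secondary criterion. The protocol text available does not mention termination of pregnancy.

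**Analysis.** Section 16.3 compares josamycin with placebo by intention to treat and reports relative risks with 95% confidence intervals.

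**The concern.** Every woman in this trial is having her fetus karyotyped, so some abnormal results must be expected among those randomised, and some of those pregnancies may be terminated. Whether that happens does not depend on josamycin.

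Section 12.1 read literally makes a termination from 22 weeks a treatment failure, and treats any other indicated preterm delivery the same way. Section 2 asks only about spontaneous prematurity. Section 12.2.1 does not say whether an induced ending at 16 to 22 weeks is a late miscarriage, so centres could code the same ending differently.

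Because terminations should occur equally often in the two blinded arms, what is at stake is dilution and an endpoint whose meaning is unclear, not confounding. A constant share of unresponsive events in both numerators moves a relative risk toward 1 and uses up power in a sample size that carries no allowance for it.

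**Working it through.** **Inputs from Protocol section 16.1.** Control risk 17%; a 50% reduction, so 8.5% on josamycin; α = 0.05; power 0.80; 238 women per group.

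**Assumptions, not in the documents.** k is the share of randomised women whose pregnancy is terminated for an abnormal karyotype, equal in both arms, taken as 1%, 3% and 5%. With 238 per arm that is 2.4, 7.1 and 11.9 women. s is the share of those terminations that fall after 22 weeks.

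**1. The plan's own figure.** Two-sided α, unpooled normal approximation:

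n = (1.96 + 0.842)² × (0.17 × 0.83 + 0.085 × 0.915) / (0.17 − 0.085)² = 237.8, so 238.

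The stated sample size reproduces. With the pooled-variance formula, 238 per arm gives 79.6% power. That is the baseline below.

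**2. Primary endpoint as worded.** A terminated pregnancy counts as an event if it ends after 22 weeks and as a non-event if it ends before:

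- placebo: p₁ = 0.17 × (1 − k) + k × s
- josamycin: p₂ = 0.085 × (1 − k) + k × s

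Example, k = 0.03 and s = 0.5: p₁ = 0.1649 + 0.015 = 0.180; p₂ = 0.0825 + 0.015 = 0.097; RR = 0.54; power 74.1%.

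| k | s = 0 (all before 22 weeks) | s = 0.5 | s = 1 (all after 22 weeks) |
|---|---|---|---|
| 1% | RR 0.50, power 79.1% | RR 0.51, power 77.8% | RR 0.53, power 76.5% |
| 3% | RR 0.50, power 78.2% | RR 0.54, power 74.1% | RR 0.58, power 70.5% |
| 5% | RR 0.50, power 77.2% | RR 0.57, power 70.4% | RR 0.62, power 64.8% |

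With s = 0 the factor (1 − k) cancels, so the relative risk is unchanged. Only the risk difference shrinks (8.5 to 8.08 points at k = 5%), and power falls by at most 79.6 − 77.2 = 2.4 points.

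**3. Would removing these women from the primary set help?** Power with early terminations kept as non-events, against power with those women removed:

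- k = 1%: 79.1% against 79.2%
- k = 3%: 78.2% against 78.4%
- k = 5%: 77.2% against 77.5%

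The gain is at most 0.3 points, and the relative risk is 0.50 either way.

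**4. Late miscarriage.** The documents give no rate for this endpoint. For illustration only, assume true risks of 2% and 1%, with 1% of women per arm terminated in the window and coded as late miscarriage. To a close approximation RR = (1 + 1) / (2 + 1) = 0.67 instead of 0.50. An uncommon endpoint is sensitive to a small number of misclassified endings.

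**The case against.** **The protocol is silent; it does not state a rule.** Nowhere does it say that terminations count as preterm deliveries or late miscarriages. The objective says spontaneous, miscarriage ordinarily means a spontaneous loss, and the text is a rough translation. This stands as a caution about intent. It does not remove the problem, because section 12.1 is the operative definition and its wording covers any premature delivery in the window.

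**Text is missing.** Section numbers jump from 8 to 12 and from 13.9 to 16.1, and section 16.3 lists exits from the protocol among the items to compare. A withdrawal rule may sit elsewhere, and finer classification may be in an analysis plan. But the eligibility, randomisation and endpoint sections are all shown, and the mismatch between sections 2 and 12.1 lies within them.

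**The size is assumed.** Neither the share nor the timing of terminations is documented. Entry is at 15 to 20 weeks and no karyotype turnaround is given, so many terminations could precede 22 weeks. At 1%, half of them late, the loss is under 2 points of power. This stands.

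**Two stronger readings are tempting, and neither is supported.** A reader might infer that terminations pull the primary effect toward the null however they are classified. Step 2 shows otherwise: counted as non-events, or as late miscarriages (which are non-events for the primary), they leave the primary relative risk at 0.50. A reader might also infer that women with an abnormal karyotype should leave the primary analysis set. Step 3 shows almost no gain, and section 16.3 specifies intention to treat. Such a set would also drop continuing pregnancies that could still respond, while keeping terminations for other reasons.

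**Conclusion.** The point holds as a mismatch between objective and endpoint, made more consequential by recruitment through karyotyping. Read literally, section 12.1 counts a termination or other indicated delivery from 22 weeks as a primary event, and section 12.2.1 leaves induced endings at 16 to 22 weeks unclassified.

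For the primary endpoint, only terminations counted as preterm deliveries attenuate the relative risk: to 0.51–0.57, with power of 78–70%, if 1–5% of randomised women are affected and half of those terminations fall after 22 weeks. These figures rest on that assumed share and timing, on equal rates in the two arms, and on the planning values in section 16.1. They cover terminations only; other indicated deliveries are not quantified. At the low end the effect is small; toward the upper end it is material. The randomised comparison itself remains valid.

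**What to change.** - In section 12.1, define the primary endpoint as spontaneous preterm delivery at 22 to 37 weeks, in line with section 2.
- Classify every pregnancy ending, blind to arm, as spontaneous delivery, indicated delivery, termination or fetal loss.
- State that terminations count in neither the preterm-delivery nor the late-miscarriage numerator, and report them by arm.
- Keep all randomised women as the primary intention-to-treat set. Add a sensitivity analysis that leaves out women with a chromosomal anomaly on the qualifying amniocentesis. Fetal karyotype is fixed before randomisation, so this restriction, applied blind to arm, does not break the randomised comparison.

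**Cost.** Endpoint wording and one coded eCRF item; section 13.8 already provides for collecting pregnancy outcome. The primary endpoint will have slightly fewer events. Section 16.1 does not say whether its 17% is limited to spontaneous deliveries, so that planning rate should be checked against the new definition.

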12.1 Primary judgment criterion

Occurrence of premature delivery between 22 and 37 weeks

12.2 Secondary judgment criteria.

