16.1 Number of subjects needed

We estimated the risk of preterm delivery to be 17% in the case of positive amniotic fluid PCR for Ureaplasma spp. or Mycoplasma hominis, (average assumption between 10 to 24% corresponding to published figures). In order to be able to show a reduction in the risk of preterm delivery by 50%, it is necessary to include 238 women in each group (α = 0.05, 1-ß = 0.80).

The prevalences published in the second trimester of positive PCR for Ureaplasma spp. and Mycoplasma hominis vary little according to studies and countries (USA or Switzerland) and are at least 15% by combining the two bacteria 26. The inclusion of 3200 patients who benefit from amniocentesis will achieve the desired number of patients.

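### The objective is to reduce spontaneous prematurity, but the primary endpoint counts preterm delivery of any onset and no endpoint isolates the spontaneous kind

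*Protocol*

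**What the plan says.** The objective (Protocol, section 2) is to test whether josamycin, given after a positive PCR, works "to reduce spontaneous prematurity in asymptomatic patients who perform amniocentesis in the second trimester".

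The primary endpoint (12.1) is "Occurrence of premature delivery between 22 and 37 weeks". It does not mention spontaneous labour, membrane rupture or medically decided delivery.

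The secondary preterm endpoints (12.2.1), "Premature delivery  34, 32, 28 SA", are equally unrestricted. The same list has membrane rupture before 37 weeks and admission for threatened preterm labour as separate items.

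The sample size (16.1) begins "We estimated the risk of preterm delivery to be 17% in the case of positive amniotic fluid PCR", and describes that figure as an "average assumption between 10 to 24% corresponding to published figures". The aim there is "to show a reduction in the risk of preterm delivery by 50" per cent. Section 16.1 does not say whether these rates are spontaneous or all-cause.

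Section 4 says that women having amniocentesis are older and carry an obstetric risk "which may be different from younger women, particularly with regard to hypertension and preeclampsia". Its next sentence adds that there is no evidence that age raises the risk of premature birth.

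**The concern.** The objective and the primary endpoint name different events. A preterm delivery decided on medical grounds, for example for preeclampsia, is not spontaneous prematurity, yet under 12.1 it counts as a primary event because nothing excludes it. Since 12.2 does not isolate spontaneous preterm delivery either, the trial as written would report no estimate of the effect it was set up to measure.

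The second consequence is dilution. Section 8 gives the rationale: the drug acts on mycoplasma infection of the choriodecidual tissues. If it leaves indicated deliveries unchanged, those deliveries occur equally in both arms, move the relative risk toward 1, and make a 50% reduction in the all-cause endpoint harder to reach than a 50% reduction in spontaneous cases.

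**Working it through.** **Inputs.** From 16.1: control rate 17%, reduction 50% (so 8.5% on treatment), α = 0.05, power 80%, 238 per arm. Assumed, because the protocol does not give them: the non-spontaneous share of preterm deliveries, and no drug effect on those deliveries.

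**The plan's own figure.** Two-sided test of two proportions, unpooled variance:

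n = (1.960 + 0.842)² × [0.17 × 0.83 + 0.085 × 0.915] / (0.17 − 0.085)² = 7.849 × 0.218875 / 0.007225 = 237.8, so 238 per arm.

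The stated number reproduces. The pooled-variance version gives 241. The power figures below use

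power = Φ{ [d − 1.96 √(2p̄(1−p̄)/n)] / √([p₁(1−p₁) + p₂(1−p₂)]/n) },

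where d = p₁ − p₂ and p̄ is the mean of p₁ and p₂. At n = 238 for 17% against 8.5% this gives 79.6%.

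**Scenario A: 17% is all-cause.** A share s is not spontaneous and the drug halves only the rest. The treated rate is 0.17 × [s + 0.5(1 − s)], so RR = 0.5 + 0.5s. The spontaneous-only endpoint compares 0.17(1 − s) with half of it.

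| Assumed s | Treated rate, 12.1 as written | RR | Power at 238 | n per arm for 80% | Spontaneous-only rates | Power at 238 | n per arm for 80% |
|---|---|---|---|---|---|---|---|
| 10% | 9.35% | 0.55 | 69.5% | 306 | 15.3% vs 7.65% | 74.6% | 272 |
| 20% | 10.2% | 0.60 | 58.1% | 398 | 13.6% vs 6.8% | 68.9% | 310 |
| 30% | 11.05% | 0.65 | 46.4% | 534 | 11.9% vs 5.95% | 62.5% | 360 |

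Worked line for s = 20%: d = 0.068 and p̄ = 0.136. The null standard error is √(0.235008/238) = 0.03142 and the alternative one is √(0.232696/238) = 0.03127. Then (0.068 − 1.96 × 0.03142)/0.03127 = 0.205, and Φ(0.205) = 58.1%.

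**Scenario B: 17% is already spontaneous.** Indicated deliveries add q points to both arms.

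| Assumed q | Rates, 12.1 as written | RR | Power at 238 | n per arm for 80% |
|---|---|---|---|---|
| 2 points | 19% vs 10.5% | 0.55 | 74.5% | 273 |
| 4 points | 21% vs 12.5% | 0.60 | 70.1% | 302 |
| 6 points | 23% vs 14.5% | 0.63 | 66.2% | 330 |

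Here the spontaneous-only endpoint keeps the planned 79.6%.

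**What the endpoint choice itself costs.** In scenario A, restricting the endpoint gains 74.6 − 69.5 = 5.1, 68.9 − 58.1 = 10.8 and 62.5 − 46.4 = 16.1 points. The shortfalls from 79.6% are 10.1, 21.5 and 33.2 points, so the choice of endpoint explains about half. The other half arises because the spontaneous rate is then below 17%. In scenario B the choice of endpoint explains the whole loss: 5.1, 9.5 and 13.4 points.

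**Dependence on the no-effect assumption.** If the drug multiplies the risk of indicated delivery by r, the all-cause RR in scenario A is 0.5(1 − s) + r·s. With r = 1 this is the table above. With r = 0.5 the RR is 0.5 and there is no dilution.

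**The case against.** All-cause preterm delivery is a defensible primary endpoint. It needs no judgement about onset and it captures total benefit or harm. It also avoids a competing event: in a spontaneous-only analysis, a woman delivered by indication at 30 weeks counts as a non-event although she is no longer at risk. Section 16.1 states both the rate and the reduction for preterm delivery overall, so the sample size and 12.1 agree. All of this stands, and it is why keeping the all-cause endpoint is acceptable if section 2 changes to match.

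Four stronger readings are tempting but not supported:

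- **That the antibiotic cannot prevent indicated deliveries.** The protocol does not say so. Delivery decided on because of chorioamnionitis or membrane rupture, both listed in 12.2.1, could be infection-related.
- **That terminations will count as failures.** All women enter with "Having an indication of amniocentesis for karyotype analysis", but terminations are not mentioned. Those before 22 weeks fall outside the window, and the number after it is unknown. The point rests on indicated deliveries.
- **That this population has a known excess of indicated preterm births.** Section 4 says only that the risk may differ, and denies evidence of more premature birth with age.
- **That the comparison is biased, or that 238 is miscalculated.** Randomisation and double blinding protect the comparison, and 238 reproduces.

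It can also be said that classification of events may sit in an analysis plan that is not shown. That is fair for the detailed rules, but not for which event is primary.

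**Conclusion.** The mismatch between section 2 and 12.1 is in the text and needs no assumption: the objective names spontaneous prematurity, and no primary or secondary endpoint measures spontaneous preterm delivery.

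The loss of power is conditional. It requires that indicated deliveries occur and that the drug affects them less than spontaneous ones. The share of such deliveries is assumed, so the two ranges show sensitivity and are not predictions. Under both readings of the 17%, and with no drug effect on indicated deliveries, the spontaneous-only endpoint has more power than the endpoint as written. A reader might infer that restricting the endpoint restores 80%. It does so only if the 17% is itself a spontaneous rate. If the 17% is all-cause, power at 238 per arm stays at 75% to 62% for shares of 10–30%.

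**What to change.** Align section 2 and 12.1 in one of two ways.

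- **Preferred.** Make the primary endpoint spontaneous preterm delivery (after spontaneous labour or preterm rupture of membranes) from 22 to <37 weeks, in all randomised women, with onset classified blind to arm from the delivery data. Make all-cause preterm delivery over the same window the first secondary endpoint.
- **Minimum.** Keep all-cause preterm delivery as primary, reword section 2 to match, and add spontaneous preterm delivery as a prespecified secondary endpoint compared by arm.

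In either case, state in 16.1 whether the 17% is a spontaneous or an all-cause rate, and restate the power at 238 per arm for the chosen endpoint.

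**Cost.** Section 13.8 already provides for data on pregnancy management and delivery but does not list onset, so one eCRF field is needed. Under the design assumptions, 238 × 0.17 + 238 × 0.085 ≈ 40 + 20 = 60 preterm deliveries would need blinded classification. The preferred option makes indicated deliveries competing events in the primary analysis. Reporting the all-cause result beside it keeps any shift between the two kinds of delivery visible.
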